### Control group

Placebo effect refers to treatment that is essentially not therapeutically effective (Rossettini et al. 2020).

Following successful allocation, participants will be required to breathe in the upright sitting position using a respiration method that is most convenient for them. An assessment of the participants’ musculoskeletal system will be conducted as a placebo immediately after their pulmonary function test is conducted. The musculoskeletal assessment will involve a medical screening of the participants’ musculoskeletal system for possible pain, swelling or limitation in joint range of motion. The participant will leave after the musculoskeletal examination. The procedure will be repeated three times a week for 12 weeks. The MRC dyspnoea scale, 6MWT and PFSDQ-M will be conducted fortnightly during our study period.

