**Method:**

Fifty-four patients aged 40 years and above with obstructive, restrictive or mixed respiratory impairments attending the respiratory clinic at the Lagos State University Teaching Hospital, Ikeja (LASUTH), will be recruited and assigned to three groups of 18 participants based on the class of respiratory impairment. Participants in each category of respiratory impairment will be subdivided into three groups. A final group of six participants per class of impairment will participate in the experiment. Our study will be a double-blind, randomised control trial with two intervention groups and one parallel placebo control group. Pulmonary function will be assessed before and after every procedure while the six-minute walk test (6MWT), Medical Research Council dyspnoea scale and the Pulmonary Functional Status and Dyspnea Questionnaire-Modified will be assessed fortnightly during our study. Data will be analysed using descriptive and inferential statistics and a repeated MANOVA; *p* < 0.05.

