## Method

### Study Design

Our study will be a parallel 12-weeks randomised control trial, involving three groups; two intervention groups (IIS and EIS) and a parallel placebo control group of participants attending the respiratory clinic at the Lagos State University Teaching Hospital, Ikeja (LASUTH).

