**FIGURE 1 F0001:**
[figure not shown]
F-test multivariate analysis of variance of within/between group interaction.

We intend to investigate the main effects, within and between interactions, for two factors, namely:

Factor A – Therapy with three levels (Therapy A, Therapy B and No Therapy)Factor B – Types of impairments (Obstructive, Restrictive and Mixed) nested within factor A

This gives 3 × 3 = 9 groups of participants from which repeated measurements are to be obtained.

We are also planning to measure three continuous outcomes at different time points of which the minimum repeated measurements are expected to be six per subject for some of the outcomes and a maximum of 36 per subject. Suppose a minimum of six repeated measures is to be obtained from each subject, in that case, it is estimated that a minimum total sample size of 51 patients is required to detect an effect size v = 0.35 with 95% confidence (5% Type I) – similar studies also expected to produce similar results about 80% of the time (Power of test 80%). In the case that during the time of data collection, the hospital experiences a high number of COPD, IPF, ILD, cystic fibrosis, thoracic cage abnormalities patients or resources permit, we are able to increase the total sample size to at most 68 subjects with a corresponding increase in the power of the test to about 95% still detecting effect sizes between 0.3 and 0.4 (see Figure 1). This translates to the possibility of recruiting between five and eight patients per group. Hence, the sample size estimates suggest that recruiting more than eight patients per group for our study will be a waste of resources.

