Following successful allocation to one of the three groups, the participants will be required to breathe in the upright sitting position before commencing the exercise using the most convenient respiration method. A volume-incentive spirometer (Coach 2 device), which enables the patient to inhale air through a mouthpiece and corrugated tubing attached to plastic bellows, will be used for the inspiratory exercise, with the volume of air displaced indicated on a scale located on the device enclosure (Kumar et al. 2016). The procedure will be demonstrated to the participant to ensure that it is well understood before commencement. After the participants have achieved the maximum volume, they will be instructed to hold the volume of air attained on the scale constant for 3–5 sec before exhalation (Zayed, Ahmed & Salem 2017). The participants will repeat the exercise three times to complete one set; three sets will be performed up to a maximum of 10 attempts. One minute of rest will be given between sets to reduce fatigue. The participants will leave after the following musculoskeletal assessment: The musculoskeletal assessment will involve screening of the participants’ musculoskeletal system for possible pain, swelling or limitation in joint range of motion. The procedure will be stopped whenever the subject feels dizziness or experience pain in the chest. The procedure will be repeated three times a week for 12 weeks. The MRC dyspnoea scale, 6MWT and PFSDQ-M will be conducted fortnightly during the study period.

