Following successful allocation, the participants will be required to breathe in the upright sitting position before commencing the exercise using the most convenient respiration method. In an upright sitting position, the participants will be asked to breathe in air through the nose to the maximum, then breathe out into a standard peak flow meter. The peak flow cursor will be adjusted to zero, and participants will be instructed to avoid touching the cursor during the exercise. The procedure will be demonstrated to the participants to ensure that it is well understood before commencement. They will be required to wrap their mouth tightly around the mouthpiece of the peak flow meter, to prevent the slippage of air around the corners of the device, then breathe out maximally into the peak flow meter as hard and as fast as possible (Adeniyi & Erhabor 2011). The effort will be noticed on the cursor. The cursor will be returned to zero, and the exercise will be repeated three times to complete one set. A total of three sets will be performed up to a maximum of 10 attempts. One minute of rest will be given between sets to reduce muscular fatigue. The procedure will be stopped if the participant feels dizziness or experiences pain in the chest. To avoid a Valsalva manoeuvre, participants will be asked not to hold their breath for more than 5 seconds following the maximum expiration. The participant will leave after the following musculoskeletal assessment. The musculoskeletal assessment will involve screening of the participants’ musculoskeletal system for possible pain, swelling or limitation in joint range of motion. The procedure will be repeated three times a week for 12 weeks. The participants MRC dyspnoea scale, 6MWT and PFSDQ-M will be conducted fortnightly during the study period.

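### The placebo is a musculoskeletal assessment that both therapy arms also receive, so the comparator is a partly contact-matched no-training control and its contrasts are not effects over placebo

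*Protocol article*

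**What the plan says.** The Abstract (Method) describes the trial as follows: "Our study will be a double-blind, randomised control trial with two intervention groups and one parallel placebo control group". Study Design repeats the label: "two intervention groups (IIS and EIS) and a parallel placebo control group".

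The Control group section says what the placebo is: "An assessment of the participants’ musculoskeletal system will be conducted as a placebo immediately after their pulmonary function test is conducted". It is a screen for pain, swelling or restricted joint movement, after which the participant leaves.

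The same screen, with the same content, closes the session in both therapy arms. For IIS: "The participants will leave after the following musculoskeletal assessment". For EIS: "The participant will leave after the following musculoskeletal assessment".

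The text after Figure 1, which defines the factors to be analysed, names the arms differently: "Factor A – Therapy with three levels (Therapy A, Therapy B and No Therapy".

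**The concern.** A placebo has to reproduce the non-specific part of the treatment it stands in for. Here the named placebo is given to everyone, so it separates no arm from any other. What separates therapy from control is the training block: the device, its demonstration, the maximal efforts with a visible reading, and the rests between sets.

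Data analysis plans independent t-tests of the study groups against control. The outcomes include the self-rated MRC dyspnoea scale and PFSDQ-M, and the effort-dependent 6MWT and forced spirometry. A difference on any of these combines a training effect with whatever attention and expectation the training block creates. Calling that difference an effect over placebo would claim a control that the design does not have. This affects two of the three pairwise arm contrasts. The Discussion expects that the findings may be recommended in clinical guidelines, so the label would matter beyond this report.

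The point is about what the comparator controls for. Who knows the allocation is a separate question.

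**Working it through.** **1. The plan's own figure.** Inputs from Sample size calculation: 9 groups, 6 measurements, f(V) = 0.35, alpha 0.05.
- s = min(9 − 1, 6 − 1) = 5
- numerator df = 8 × 5 = 40
- denominator df = 5 × (51 − 9 − 5 + 5) = 210
- λ = 51 × 5 × 0.35² = 31.2375

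The critical F is 1.4522 and the power 0.8011, as stated; N = 50 gives 0.789. The calculation reproduces, and none of its inputs depends on what the control is called.

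**2. Arm contents, from the IIS, EIS and Control group sections.**

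| Component | IIS | EIS | Control |
|---|---|---|---|
| Three visits a week for 12 weeks | yes | yes | yes |
| Comfortable upright breathing | yes | yes | yes |
| Musculoskeletal assessment | yes | yes | yes (named placebo) |
| Fortnightly MRC, 6MWT, PFSDQ-M | yes | yes | yes |
| Training block | volume spirometer | peak flow meter | none |

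Every shared row drops out of a between-arm difference. IIS − control and EIS − control each leave the training block against nothing. IIS − EIS leaves one training block against another with the same number of sets, attempts and rests.

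**3. Amount of training and of shared spirometry.**
- Sessions: 3 × 12 = 36.
- Device efforts per session: 3 sets × 3 = 9, with a maximum of 10. Over 36 sessions that is 9 × 36 = 324 to 10 × 36 = 360 in each therapy arm, and none with a training device in control.
- Spirometry: the Abstract has pulmonary function assessed before and after every procedure, and the Spirometry section has three tests with at most eight attempts. If this applies to every arm, each participant, controls included, makes 2 × 3 = 6 to 2 × 8 = 16 forced manoeuvres per visit, or 216 to 576 over 36 visits.

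So controls also meet a breathing device and maximal effort at each visit. That too is common to all arms and cancels.

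**4. Illustration of size.** The documents give no expectation effect. Assume that attention and expectation alone shift an outcome by d standard deviations and that the device itself does nothing. For a two-sided independent t-test at 0.05 with n per arm, the rejection rate comes from the non-central t distribution with 2n − 2 df and non-centrality d√(n/2). The Abstract gives 6 participants per arm within an impairment class, and 3 × 6 = 18 per arm when classes are pooled.

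| d (assumed) | 18 versus 18 | 6 versus 6 |
|---|---|---|
| 0.1 | 6.0% | 5.3% |
| 0.2 | 9.0% | 6.1% |
| 0.3 | 14.1% | 7.6% |
| 0.5 | 30.8% | 12.3% |

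The nominal rate is 5%. Data analysis does not say whether the t-tests pool the classes, so both columns are shown.

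**The case against.** The strongest reply is that the control is far from empty. It has the same visits, the same assessment and, as the text reads, repeated forced spirometry at each visit. The EIS exercise, a full breath in followed by a forced breath out into a peak flow meter, closely resembles that manoeuvre. The text says the training is demonstrated; it does not say that efforts are coached. Data analysis mentions a physiotherapist supervising each participant's group and makes no exception for control. All of this stands. A reader might infer that controls receive nothing resembling the therapy sessions, and the documents do not support that.

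Second, No Therapy might mean only no active therapy, which would fit the article's description of placebo as something not therapeutically effective. That softens the clash of labels. It does not change the fact that the assessment is common to all arms.

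Third, the objectives speak of the effect of each technique and nowhere promise an effect over placebo, and the clinical implication concerns IIS against EIS. This limits the harm. Even so, the placebo label is part of the design statement in the Abstract and Study Design, and the study-versus-control tests are planned.

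Fourth, spirometry is done by a blinded technician under acceptability and repeatability criteria, and the 6MWT is done without encouragement. These safeguards reduce assessor influence and may make a given shift less plausible for those outcomes. They do not remove the participant's own expectation or effort.

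**Conclusion.** The concern holds in a limited form. The design has a partly contact-matched no-training control, and the placebo label describes a property it does not have. IIS-control and EIS-control are valid randomised contrasts of training against no training, but they include any attention and expectation effect of the training block. They cannot be reported as effects over placebo. This matters most for the MRC scale and PFSDQ-M, and then for the 6MWT and spirometry. IIS-EIS does not depend on the label, and the sample size of 51 is unaffected.

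This conclusion follows from the arm descriptions alone. The rejection rates, about 6% to 31% at 18 versus 18 for 0.1 to 0.5 SD and about 8% to 12% at 6 versus 6 for 0.3 to 0.5 SD, rest on an assumed shift and a device with no effect. They show how the problem would scale and are not an estimate of its size here.

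Two stronger readings are tempting. One is that the therapy-control comparisons are invalid. They are not, because randomisation still supports training against no training. The other is that the trial needs a sham device. The documents do not require one, and adding one would be a design trade-off; an accurate label and interpretation are enough to correct the error.

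**What to change.** In the Abstract (Method), Study Design and Control group sections, replace the placebo control wording with: no-training control with the common musculoskeletal assessment. This agrees with the No Therapy level in the sample size text.

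In Data analysis, add that IIS-control and EIS-control differences estimate training plus any attention and expectation that goes with it. Add also that the IIS-EIS contrast is the better matched one for the device comparison named under Clinical implication.

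This needs no extra patients, staff or procedures, and no sample size input changes. The cost is a less favourable description of the design and a narrower claim for the therapy-control results.

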### Spirometry

The assessment will be conducted by a technician certified by the Pan African Thoracic Society, blinded to group allocation. A portable spirometer (Koko SX 1000 Standalone Version 7 Pneumotach) will be used for this assessment. Daily calibration of the device will be conducted using a 3.0-L syringe. A brief description of the assessment procedure and technical steps to obtain pulmonary function data and variables will be explained to each participant. After 2–3 tidal breaths, participants will be asked to inhale deeply to total lung capacity and then exhale rapidly (without any pause) through a disposable mouthpiece until as much air as possible has been expelled. The test will be performed in a sitting or standing position. The assessments will be repeated three times after adequate rest. The maximum number of attempts permitted will be eight. Following the fulfilment of acceptability and repeatability criteria, the two best curves and two best tests will be selected. The average values of the FVC and FEV_1_ will be recorded (Hall & Stanojevic 2019).

### Six-minute walk test

The 6MWT is a valid, responsive and reliable outcome measure frequently used in cardiac and pulmonary rehabilitation. It is often used to determine functional exercise capacity in patients undergoing cardiorespiratory rehabilitation. In a review of 167 articles between 1948 and April 2011 through Ovid MEDLINE, SPORTS, EMBASE, CINAHL, Cochrane reviews and Cochrane clinical trial, it revealed a responsiveness of the 6MWT in cardiac rehabilitation with an estimated mean difference of 60.43 m (95%, confidence interval 54.57 m – 66.30 m; *p* < 0.001) and moderate evidence of repeatability (Bellet, Adams & Morris 2012). A study by Brown and Nathan (2018) revealed a strong correlation between clinical outcomes and 6MWT distance in patients with chronic respiratory diseases.

The 6MWT will be performed according to the standardised procedure, and the first author (PI) who will be blinded to group allocation will supervise the process. The participants will be asked to walk at their maximum pace along a 30 m-long straight road. They will not be given any encouragement; the patient’s symptoms may limit the test. Therefore, if there are any signs of significant distress, such as dyspnoea, dizziness, angina or skeletal muscle pain, the participant will be asked to stop and sit down. The participants will only be allowed to continue upon alleviation of the discomfort. The total distance the participants cover will be recorded in meters (Du Bois et al. 2011). The procedure will be repeated at a 2-week interval for the duration of our study.

### Medical Research Council dyspnoea scale

The MRC breathlessness scale quantifies the disability associated with breathlessness by identifying if breathlessness occurs when it should not (Grades 1 and 2) or by quantifying the associated exercise limitation (Grades 3–5) (Stenton 2008). Mahler and Wells (1988) reported a 98% agreement between observers recording MRC breathlessness scores. In a statement by the ATS, the score correlates well with the results of other breathlessness scales, lung function measurements and direct measures of disability such as walking distance (stats.oarc.ucla.edu). The MRC breathlessness scale is commonly used to describe patient cohorts and stratify them for pulmonary rehabilitation interventions, predict survival and use as complementary to FEV_1_ in describing disability in those with COPD and other forms of respiratory impairments (Bestall et al. 1999; Nishimura et al. 2002; Wedzicha et al. 1998).

The instrument has five statements that describe the range of respiratory disability. Depending on the literacy of the participants, the instrument can either be self or interviewer administered; RA2 will explain the content of the instrument to the participants prior to its administration. Participants will be encouraged to clarify issues related to the instruments before submitting their responses. The instrument will be administered at our study site at 2 week intervals during the study period. They will be comfortably seated on a chair without wheels, and the research instrument and writing materials placed on a desk. The RA2 will carefully introduce the research instrument to the participants, explain the domains and indicate the options stated on the instruments. Respondents will be informed to seek clarification on the instruments whenever required from either the PI or RA2, both blinded to group allocation.

### Pulmonary functional status and dyspnea questionnaire

The pulmonary functional status and dyspnea questionnaire (PFSDQ) is a self-administered questionnaire with 164 items designed to assess the level of dyspnoea and activities in respiratory conditions (Meek & Lareau 2003). The modified version of the PFSDQ-M is a shorter version of the instrument consisting of 40 items that evaluate dyspnoea, fatigue and levels of activity (Lareau, Meek & Roos 1998).

The PFSDQ and PFSDQ-M questionnaires evaluate dyspnoea independent of activities with five items that evaluate dyspnoea. Pulmonary functional status and dyspnea questionnaire measures dyspnoea associated with 79 activities. Pulmonary functional status and dyspnea questionnaire-modified measures dyspnoea associated with 10 activities (Meek & Lareau 2003).

The PFSDQ has good test–retest reliability, r = 0.94 on the dyspnoea scale and internal consistency of α = 0.88 to 0.94, while PFSDQ-M has a test–retest reliability on the dyspnoea scale of r = 0.83 and internal consistency of α = 0.94 (Lareau et al. 1998). The PFSDQ has been shown to be responsive over time, while the PFSDQ-M has been shown to be more responsive to change following pulmonary rehabilitation (Lareau et al. 1999).

The PFSDQ-M evaluates the effect of dyspnoea, fatigue and changes experienced in activities of daily living (ADL), the dyspnoea and fatigue domain of the instrument has five general items and 10 specific items, while the change experienced by patients has 10 specific items (Lareau et al. 1998). Participants are expected to assign a score according to their experience using a scale of 0–10 on the specific item scale for dyspnoea and fatigue with 0 score indicating no interference; 1–3 indicates mild interference; 4–6, moderate interference; 7–9 severe interference and 10 as extreme interference (Kovelis et al. 2008). For the third domain, participants are also required to quantify on a scale of 0–10 with 0 indicating as active always; 1–3 indicates slight change; 4–6 indicates moderate change; 7–9 indicates extreme change, while 10 indicates patient can no longer perform the activity (Kovelis et al. 2008). A partial score of 0 to 100 will be calculated for each domain while the overall score will be 0–300, with a higher value indicating the severity of activity limitation. The instrument will be administered every 2 weeks during our study period. Participants will be comfortably seated on a chair without wheels and the research instrument and writing materials will be placed on a desk. The RA2 will carefully introduce the research instrument to the participants, explain the domains and indicate the options stated on the instruments. Respondents will be informed to seek clarification on the instruments whenever required from either the PI or RA2, blinded to group allocation.

### Data analysis

The Statistical Package for Social Sciences (SPSS Inc, Chicago, Illinois, United Sates) version 26.0 for windows package programme will be used to analyse data. Descriptive statistics of mean, standard deviation, frequencies and percentages will be used to summarise the results. Bar charts, pie charts and histograms will be utilised for pictorial illustration. A multivariate analysis of variance (MANOVA) will be used to compare the outcome pulmonary function variables (FEV_1_, FVC, FEV_1_/FVC, PEFR) and QoL (6MWT, MRC dyspnoea scale score and PFSDQ-M score) among groups, while the Bonforreni’s *t*-test will be utilised for post hoc analysis to detect where significant changes occurred in the outcome variables. Dependent t-tests will be used to compare the pre- and post-test results within variables while independent t-tests will be used to compare the outcome variable among the study and control groups. The level of significance will be set at *p* ≤ 0.05.

The study does not potentially involve risk or harm, as all interventions can only be performed within the limit of the patient’s tolerance. However, participants may experience mild discomfort because of the exercise, including temporary muscle soreness, increased heart rate, blood pressure, sweating and dizziness. All necessary care will be in place to prevent the occurrence of any adverse event. However, in case of a report of serious adverse events (e.g. comorbidities, injuries, persistent excruciating pain, dizzy spells, headache, etc.) after the intervention or at any point during the trial, we would consider unblinding the participant to the intervention for their safety. Additionally, the participants will be instructed to report adverse events to the first author PI or the physiotherapist supervising their group. To ensure adequate supervision, participants per group to be attended in a day will be limited to a maximum of three. Arrangements will be made with the Accident and Emergency units of the research site to provide a standby medical team. The University of KwaZulu-Natal insurance scheme on clinical trials has fully covered participants in this type of study.

To promote participant retention, prevent loss to follow-up, compensate for time, inconveniences and expenses, participants with financial challenges accessing our study site will be granted a financial remuneration following international ethical guidelines and the South African Department of Health framework guidelines. The payment will be commensurate with the unskilled labour rate recommended by global ethics and South African guidelines (Ndebele et al. 2014). As our study is to be performed in Nigeria, Nigerian regulations regarding patient compensation will be considered. In Nigeria, unlike in South Africa, there is no minimal benchmark for payment of research participants; however, the *Labour Act* stipulates a minimum wage of 30 000.00 naira (Nigerian naira) per month to all unskilled workers, which is equivalent to $85.00 and amounts to $4.50/day. This amount was considered fair and reasonable by the Research Ethical Committee (REC) of UKZN, and the hospital facilities used as our study setting in Nigeria.

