### Sample size calculation

The pulmonary function test is the primary outcome of interest for our study and the expected clinically relevant difference for obstructive restrictive and mixed impairment using LLN and GLI reference equation as proposed by Quanjer et al. (1993). Therefore, the sample size (*n*) will be determined using G-Power statistics software (stats.oarc.ucla.edu). The power is selected at 95% = 0.95, confidence level at 5% = 0.05 and effect size of 0.35 (Figure 1), namely:

**F-tests – MANOVA:** Repeated measures, within-between interaction

**Options:** Pillai V, O’Brien-Shieh Algorithm

**Analysis:** A priori: Compute required sample size

**Input:** Effect size f(V) = 0.35

    α err prob = 0.05

    Power (1-β err prob) = 0.8

    Number of groups = 9

    Number of measurements = 6

**Output:** Non-centrality parameter λ = 31.2375000

     Critical F = 1.4522092

     Numerator degree of freedom (*df*) = 40.0000000

     Denominator df = 210

     Total sample size = 51

     Actual power = 0.8010637

     Pillai V = 0.5456570

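### Therapy is compared with control twice for each variable, once with Bonferroni correction and once by independent t-tests that carry only the common 0.05 level, so one contrast can be significant by one route and not by the other

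*Protocol article*

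**What the plan says.** The trial has three arms: inspiratory incentive spirometry (IIS), expiratory incentive spirometry (EIS) and a placebo control (Study Design). They are crossed with three impairment classes, which makes nine cells (Sample size calculation). Recruitment is 54 patients, 18 per class, with six per cell (Abstract, Method). Pooled over classes, that is 18 per arm.

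The Data analysis section sets out two between-group routes in consecutive sentences.

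- **Route 1.** A MANOVA compares seven outcomes among groups (FEV1, FVC, FEV1/FVC, PEFR, 6MWT, MRC score, PFSDQ-M score). A Bonferroni t-test then "will be utilised for post hoc analysis to detect where significant changes occurred in the outcome variables".
- **Route 2.** In the protocol's words, "independent t-tests will be used to compare the outcome variable among the study and control groups".

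One sentence then covers everything: "The level of significance will be set at" p ≤ 0.05. The section does not rank the two routes, call either one descriptive, or make the t-tests conditional on the MANOVA. The Abstract names a repeated MANOVA and p < 0.05 and gives no order either.

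**The concern.** A post hoc test after a comparison among three arms takes in IIS against control and EIS against control. The independent t-tests address the same contrasts for the same variables. Bonferroni is attached only to the post hoc step, so a p-value between the corrected level and 0.05 is not significant by one route and significant by the other. The two verdicts differ in significance, not in the direction of the effect.

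The trial wants to say which therapy suits which impairment (Abstract, Clinical implication; Background) and hopes to inform clinical guidelines (Discussion). Those statements rest on these contrasts. If the t-test may support them, the error rate behind a claim is that of the t-test, whatever correction the preceding sentence announces. The point concerns repeated testing of one contrast within one variable. It does not concern the number of outcome variables.

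**Working it through.** **Inputs from the protocol article.** From the Sample size calculation: "α err prob = 0.05", "Power (1-β err prob) = 0.8", "Effect size f(V) = 0.35", "Number of groups = 9", "Number of measurements = 6". From the design: three arms, 18 per arm pooled over classes, 6 per cell.

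**Assumptions.** Normal data, equal variances, two-sided tests. A true difference of 0.8 SD is used where power is needed, because the article gives no difference or SD for any single outcome. The post hoc family is not listed, so it is taken as 3 pairs (the three arms) up to 36 pairs (all nine cells, 9 × 8/2).

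**Step 1. The plan's own figure.** For the within-between MANOVA with Pillai's V:
- s = min(9 − 1, 6 − 1) = 5
- V = s·f²/(1 + f²) = 5 × 0.1225/1.1225 = 0.5457
- λ = s·f²·N = 5 × 0.1225 × 51 = 31.2375
- df = 8 × 5 = 40 and 5 × (51 − 9 − 5 + 5) = 210
- critical F = 1.4522, power = 0.8011

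The stated total of 51 is reproduced. It concerns the interaction test and says nothing about either set of pairwise tests.

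**Step 2. Thresholds.** The independent t-test uses its own two groups. The post hoc test uses the pooled error of the model.

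| Contrast | t-test at 0.05 | Bonferroni, 3 pairs (0.05/3 = 0.0167) | Bonferroni, 36 pairs (0.05/36 = 0.0014) |
|---|---|---|---|
| 18 v 18 | 2.03 (34 df) | 2.48 (51 df, three arms) | does not apply |
| 6 v 6 | 2.23 (10 df) | 2.49 (45 df, nine cells) | 3.41 (45 df, nine cells) |

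Thirty-six pairs exist only among the nine cells of 6, so that correction is not applied to the pooled 18 v 18 contrast.

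**Step 3. False positives within one variable, no true effect** (simulation, 200,000 runs).
- Two therapies against a shared control, t-tests at 0.05: 9.1% with 18 per arm. Independent contrasts would give 1 − 0.95² = 9.75%; the shared control lowers it slightly.
- The same two contrasts, Bonferroni over 3 pairs: 3.1%.
- A claim allowed if either route is significant: 9.0%, the same as the t-tests alone to within simulation error.
- Six t-tests within the three classes (6 v 6), taken as one family: 24.9%. Independence would give 1 − 0.95⁶ = 26.5%.

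**Step 4. How often the routes disagree on one contrast, true difference 0.8 SD.**

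| Setting | t-test alone significant | Bonferroni alone significant | Disagree |
|---|---|---|---|
| 18 v 18, 3 pairs | 16.8% | 0% | about 17% |
| 6 v 6, 3 pairs | 10.6% | 1.0% | about 12% |
| 6 v 6, 36 pairs | 21.3% | below 0.01% | about 21% |

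At 18 v 18 with 3 pairs, disagreement is 3.3% under the null, 13.4% at 0.5 SD and 13.0% at 1.0 SD.

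**The case against.** The strongest case on the other side is that the article does signal a lead analysis. The sample size is computed for the repeated-measures MANOVA and the Abstract names only that method, so the t-tests may be meant as supplementary. A ranking of tests is often left to a statistical analysis plan, which is not shown. The post hoc sentence lists no contrasts and could also refer to time points. The t-test sentence does not say that no correction applies.

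Part of this stands. That the t-tests are uncorrected is an inference, and so is the exact post hoc family. The rest does not remove the point. A missing ranking alone would be no finding, but here the article commits to two tests of study against control, and Bonferroni is attached to only one. Powering the MANOVA does not settle which pairwise result supports a claim.

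Three stronger readings are tempting, and the documents do not support them.

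- **That the correction has no force.** This holds only if significance by either route counts as a claim. The article does not say so, though it does not exclude it.
- **That the t-test is always the more favourable.** With 6 per cell, pooled error on 45 df and 3 pairs, Bonferroni alone is significant in about 1% of runs, roughly one disagreement in eleven (1.0/11.6).
- **That the routes disagree on nearly half of contrasts.** That figure comes from putting a 36-pair correction on the pooled 18 v 18 contrast. The 36 pairs belong to cells of 6, where the gap is about 21%.

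**Conclusion.** The point holds as a conflict between two stated decision rules. If the independent t-tests may support a claim, the chance of at least one false positive per variable is about 9% for two therapies against control, where Bonferroni over 3 pairs would give about 3%. The 25% figure needs two further conditions: that the t-tests are run within class, and that the three classes form one error family. The article states neither, although its 3 × 3 design and class-specific aim make within-class testing plausible.

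The disagreement rates of about 17% (18 v 18) and 12% to 21% (6 v 6) rest on the assumed 0.8 SD and on pooled error in the post hoc test. The 9%, 3% and 25% do not depend on the assumed difference. The matter should be corrected before analysis. It does not affect the validity of the MANOVA itself or the reproduced sample size.

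**What to change.** Delete the sentence on independent t-tests, or keep the tests and label them descriptive, with no claim to rest on them. Then state four things:

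1. Each between-group contrast is estimated once, from the fitted model.
2. The contrasts are listed: IIS against control, EIS against control and IIS against EIS, overall and within each impairment class. The class-specific contrasts are needed because the aim is to find the more suitable therapy for each class.
3. The multiplicity correction is applied once over that listed family.
4. The corrected result decides.

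The edit is a few sentences and needs no extra patients or visits. The cost is that some nominally significant results will be lost. With all 12 contrasts per variable in one family (3 overall and 3 × 3 within class), Bonferroni sets the level at 0.05/12 = 0.0042, which is demanding with 6 per cell.
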